**8.3 Cost-effectiveness analyses**

An economic evaluation will be performed from the societal perspective and in accordance with the intention-to-treat principle. All costs and consequences relevant to the intervention will be taken into account. Intervention costs will be estimated using a micro-costing approach. Retrospective cost questionnaires will be administered at 4 weeks, and at 3 and 6 months follow-up to collect data on healthcare utilization (for example visits to general practitioner, physiotherapy, exercise therapy, rehabilitation, social work, medication), the use of informal care, absenteeism, presenteeism, and unpaid productivity losses. Resource use will be valued in accordance with the Dutch manual of costing of the Netherlands Health Institute (Zorginstituut Nederland). Missing data will be imputed using multiple imputation by chained equations(30). Incremental Cost Effectiveness Ratios (ICERs) will be calculated by dividing the difference in costs by that in effects. We will perform a cost-utility analysis with QALYs as outcome. In order to account for the possible clustering of data, analyses will be performed using linear multilevel analyses(31). Accounting for the possible clustering of data (e.g. at the hospital level) is very important, as most economic evaluations fail to do so, whereas

ignoring the possible clustering of data might lead to inaccurate levels of uncertainty and inaccurate point estimates(31). Bootstrapping techniques will be used to estimate the uncertainty surrounding the cost-effectiveness estimates. Uncertainty will be shown in cost-effectiveness planes and cost-effectiveness acceptability curves, and sensitivity analyses will be performed to test the robustness of the study results(32–34).

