## 1. INTRODUCTION AND RATIONALE

Annually approximately 21.000 patients are admitted to a hospital in the Netherlands with a hip fracture(1). It is the most devastating fracture in the elderly and is associated with excessive utilization of health care resources. The tendency to fall is prominent among elderly and increases with age and frailty level. After a first hip fracture, patients are at increased risk for recurrent falls and prone for additional injuries. This results in impairment of postoperative rehabilitation and increased morbidity and total health-care costs(2). Furthermore, the increased morbidity strongly affects the patients' health related quality of life (HRQoL)(3).

In the treatment of hip fractures, hemiarthroplasty is a commonly used procedure. Different surgical techniques are described in the literature. However, in the Netherlands the two main surgical approaches for hemiarthroplasty are the posterolateral lateral and the direct lateral approach(4).

When inserting a hemiarthroplasty through the posterolateral approach (PLA), the surgeon performs a posterior capsulotomy. During the PLA the hip abductors are protected and preserved preventing limping. However, due to inadequate posterior capsule support there is an increased risk of dislocations(5–10). The direct lateral approach (DLA) involves an incision of the gluteus medius and vastus lateralis muscles. This frequently leads to abductor insufficiency resulting in limping after surgery(11,12). However, in the DLA the posterior capsule is preserved preventing dislocation.

Currently there is no conclusive evidence of which of these two approaches results in the better patient outcomes. The PLA is assumed to be beneficial regarding HRQoL and some studies report that patients operated with PLA are more satisfied and experience less pain after a hemiarthroplasty (13–15). The presumably faster rehabilitation and better balance due to the scatheless gluteus musculature in patients treated using the PLA may be counterbalanced by the increased risk of dislocation. On the contrary, the loss of abductor muscle strength after hemiarthroplasty through the DLA can hypothetically lead to a loss of balance which intensifies the risk of falling and can result in less mobile patients. The increased immobility in the already vulnerable elderly patients will lead to higher risk of falling, asks more of caregivers and patients will rely more on home care facilities.

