### **Baseline assessment**

At baseline we will assess the EQ-5D-5L, the ADL functionality (KATZ), pre-mobility score and the living status using the Dutch Hip Fracture Audit (DHFA) registration. The assessment of the above outcomes is based on the health status prior to the trauma.

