### **Follow-up data collection**

The baseline and follow-up assessment will be conducted by the coordinating research team of the OLVG. There are three follow-up moments at 4 weeks, 3 and 6 months postoperative. The primary outcome measurement EQ-5D-5L and the secondary outcomes FES-I scale will be assessed through questionnaires online, by hardcopy or by phone at baseline, 3 and 6 months postoperatively. The health care utilization questionnaire will be assessed at 4 weeks, 3 and 6 months follow-up. The questionnaires will be handed out by the coordinating researcher. Other secondary outcome measurements (e.g. KATZ, mobility score, complications, re-operations) are detailed in the DHFA at baseline and 3 months post-operatively and will be assessed through questionnaires online, by hardcopy or by phone at 6 months after surgery and will be handed out by the coordinating researcher.

The assessment of the Short Physical Performance Battery (SPPB) balance test, which is not included in the DHFA, will be performed by one of the study researchers or nurse practitioner to protect continuity and feasibility and will only be assessed in patients included in the RCT. The SPPB will not be assessed in all patients, but in a subgroup of the patient population because the sample size is smaller. The SPPB is a group of measures that combines the results of the gait speed, chair stand and balance tests.(24)

The follow-up questionnaires will contain:

- Health-related quality of life as measured by the EQ-5D questionnaire. The EQ-5D-5L is a descriptive system of health-related quality of life states consisting of five dimensions (mobility, self-care, usual activities, pain/discomfort and anxiety/depression)(25).
- The Katz Index of Independence in Activities of Daily Living, the Katz ADL, is an instrument to assess functional status as a measurement of the client's ability to perform activities of daily living independently consisting six functions (bathing, dressing, toileting, transferring, continence and feeding)(26).
- The Falls Efficacy Scale-International (FES-I) is a short, easy to administer tool that measures the level of concern about falling during social and physical activities inside and outside the home whether or not the person actually does the activity(27).
- Additionally injuries as a result of falling and other (indication to) re-interventions

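### The 6-month QALY has no post-operative utility before 3 months, because the existing 4-week contact collects health care use but not the EQ-5D-5L

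*Protocol*

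**What the plan says.** - **Economic outcome (Protocol 8.3).** "We will perform a cost-utility analysis with QALYs as outcome". The section does not say how utilities are joined over time.
- **EQ-5D-5L schedule (6.4, Follow-up data collection).** It is obtained through "questionnaires online, by hardcopy or by phone at baseline, 3 and 6 months postoperatively". The table in 6.4 agrees: EQ-5D appears under baseline, 3 months and 6 months, and not under 4 weeks.
- **Meaning of the baseline value (6.4, Baseline assessment).** "The assessment of the above outcomes is based on the health status prior to the trauma".
- **Contacts (6.4, Follow-up data collection).** "There are three follow-up moments at 4 weeks, 3 and 6 months postoperative". In the 6.4 table the only instrument listed at 4 weeks is the health care utilisation questionnaire, completed by patient or proxy. The text confirms its timing: "The health care utilization questionnaire will be assessed at 4 weeks, 3 and 6 months follow-up".
- **Costs (8.3).** "Retrospective cost questionnaires will be administered at 4 weeks, and at 3 and 6 months follow-up".
- **Expected early course (section 1).** The rationale refers to "The presumably faster rehabilitation and better balance due to the scatheless gluteus musculature in patients treated using the PLA" and continues that this "may be counterbalanced by the increased risk of dislocation".

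**The concern.** The baseline EQ-5D-5L precedes both the injury and the treatment, so it cannot carry a treatment effect. The first utility that can differ because of the surgical approach is the one at 3 months, halfway through the 26-week horizon. Whatever happens between surgery and that point enters the QALY only through the 3-month value.

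The protocol's rationale makes early recovery a plausible place for the approaches to differ, and in both directions: faster rehabilitation with the posterolateral approach (PLA), or more dislocations. The cost side has a 4-week measurement and the effect side does not. At stake is the incremental QALY, the denominator of the incremental cost-effectiveness ratio (ICER). The gap lies in data collection, so no later analysis plan can recover it. Imputation or sensitivity analysis could only replace the missing utility by assumption.

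**Working it through.** The protocol states no QALY figure, so there is nothing of its own to reproduce. The check compares the planned schedule with the same schedule plus a 4-week value.

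**Inputs from the protocol.** EQ-5D-5L at 0, 13 and 26 weeks (6.4), a contact at 4 weeks (6.4), and a minimal clinically important difference of 0.08 (4.4).

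**Assumptions.** A trapezoidal area under the curve, equal mean baselines in the two arms, and all EQ-5D differences and utility levels used below. The 0.08 is the protocol's figure, but its placement in time is assumed.

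**Weight of each measurement in the 6-month QALY (years).** Each value is weighted by half the length of the intervals next to it.

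- Planned: baseline (13/52)/2 = 0.125; 3 months (26/52)/2 = 0.250; 6 months (13/52)/2 = 0.125.
- With 4 weeks: baseline (4/52)/2 = 0.0385; 4 weeks (13/52)/2 = 0.125; 3 months (22/52)/2 = 0.2115; 6 months 0.125.

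Of the planned total weight of 0.5, a quarter (0.125) sits on the pre-fracture value.

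**Incremental QALY.** Let d4, d3 and d6 be the EQ-5D differences, PLA minus direct lateral, at 4 weeks, 3 months and 6 months.

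- Planned: 0.250·d3 + 0.125·d6
- With 4 weeks: 0.125·d4 + 0.2115·d3 + 0.125·d6
- With 4 weeks minus planned: 0.125·d4 − 0.0385·d3

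The last line is zero only when d4 = (4/13)·d3, that is, when the difference grows linearly from zero to 3 months. For d3 = 0.08 this means d4 = 0.0246.

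| d4 / d3 / d6 (assumed) | Planned | With 4 weeks | Effect of the gap |
|---|---|---|---|
| 0.08 / 0 / 0 | 0.000 | 0.010 | all lost |
| 0.08 / 0.04 / 0 | 0.010 | 0.0185 | 46% lost |
| 0.08 / 0.08 / 0.08 | 0.030 | 0.0369 | 19% lost |
| 0.04 / 0.06 / 0.08 | 0.0250 | 0.0277 | 10% lost |
| 0.0246 / 0.08 / 0.08 | 0.030 | 0.030 | none |
| −0.04 / 0.04 / 0.08 | 0.0200 | 0.0135 | PLA overstated by 0.0065 |

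Worked example, last row. Planned: 0.250 × 0.04 + 0.125 × 0.08 = 0.010 + 0.010 = 0.0200. With 4 weeks: 0.125 × (−0.04) + 0.2115 × 0.04 + 0.125 × 0.08 = −0.0050 + 0.0085 + 0.0100 = 0.0135.

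For a fixed cost difference the ICER changes inversely with the QALY difference. A constant 0.08 makes the planned ICER 0.0369/0.030 = 1.23 times the one with 4-week data. The last row makes it 0.0135/0.0200, about 0.67 times.

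**Absolute level.** Assume utilities of 0.70 before fracture, 0 to 0.2 just after it, 0.30 to 0.45 at 4 weeks, 0.55 at 3 months and 0.60 at 6 months. The planned curve gives 0.125 × 0.70 + 0.250 × 0.55 + 0.125 × 0.60 = 0.300. A curve that starts from the post-fracture value and includes 4 weeks gives 0.229 to 0.255, so the planned level is too high by about 0.045 to 0.071. Adding 4 weeks but still starting at 0.70 gives 0.256 to 0.275, so the 4-week value alone closes only part of the gap. Any starting value common to both arms cancels in the difference, so the table above does not depend on it.

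**The case against.** Several objections carry weight.

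- **The rule is inferred.** Section 8.3 does not say how QALYs are computed, and that detail may properly sit in an analysis plan. This stands, and the trapezoid is marked as an assumption. It does not close the gap, since any rule would lack a post-operative utility before 3 months.
- **The direction is unknown.** A reader might infer that the plan hides an early gain for PLA and so makes its ICER too large. The documents do not support that. Section 1 only presumes faster rehabilitation, does not say when before 3 months it would show, and at once sets dislocation risk against it. Depending on the path, the planned data can understate, match or overstate the PLA increment.
- **The inflated level cancels.** A reader might infer that starting from pre-fracture health distorts the ICER. With equal baselines it does not, because the ICER uses only the between-arm difference.
- **The horizon is the same.** A reader might infer that costs and effects cover different periods. Both run from surgery to 6 months; the effect side is only measured more coarsely in the first half.
- **The remedy is partial.** A 4-week EQ-5D-5L does not measure the fracture, the operation or the first days. This stands, so the fix must say how that interval is valued.
- **Scope.** Only a secondary, economic outcome is affected, and the protocol does not contradict itself here. This stands, and it limits the weight of the point without removing it.

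**Conclusion.** The point holds as a weakness in data collection for the economic evaluation. The planned schedule has no post-operative utility for the first 13 of 26 weeks, and early differences between the approaches reach the QALY only so far as they are still present at 3 months.

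The size depends on the unknown path. In the scenarios shown, the share of a PLA gain that is lost runs from none (linear growth to 3 months), through 10%, 19% and 46%, to all of it (a gain gone by 3 months). With an early PLA deficit that reverses, the planned data overstate the increment: 0.0200 against 0.0135. Neither a single percentage nor a single ICER multiplier is justified, and the sign of the error is unknown. These figures rest on the trapezoidal rule, equal baselines and assumed EQ-5D differences.

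This is a cheap and worthwhile improvement. It is not a threat to the main result, because the 6-month primary endpoint is measured as planned.

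**What to change.** 1. Add the EQ-5D-5L to the 4-week questionnaire, both in the 4-week column of the 6.4 table and in the follow-up data collection text.
2. In 8.3, state that the QALY curve uses the 4-week, 3-month and 6-month values, and adjust the incremental QALY for pre-fracture EQ-5D-5L as a covariate in place of using it as the starting health state.
3. State how weeks 0 to 4 are valued, for example by one common assumed post-fracture utility in both arms, varied in the sensitivity analyses that 8.3 already foresees.

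The cost is five extra items for the patient or proxy at a contact that already takes place, plus a minor amendment. No visit is added and the primary endpoint does not change. The first days after fracture remain unmeasured, so the absolute QALY still rests partly on the assumed starting value. For patients already past 4 weeks when the change is made, the value cannot be recovered.

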## **9. ETHICAL CONSIDERATIONS**

### **9.1 Regulation statement**

The study will be conducted according to the principles of the Declaration of Helsinki, as amended in Seoul and Fortaleza (64th WMA General Assembly, October 2013)(35) and in accordance with the Medical Research Involving Human Subjects Act (WMO) and other guidelines, regulations and Acts.

### **9.2 Recruitment and consent**

Every patient with a hip fracture which should be treated with a hemiarthroplasty will be invited for study entry. Information will be given through the patient information letter and patients are able to ask questions to the treating physician or investigator. Their consent will be asked by the treating physician. In case of incapacitated subjects (i.e. elderly with cognitive impairment such as dementia), informed consent will be received by proxy through the legally representative or a family member. A copy of the signed informed consent form will be given to the patient/proxy as a separate document together with the patient information letter. Until the moment of surgery, patients will have the time to reconsider their decision. Normally, patients with hip fractures are treated in 24 hours after admission to the emergency room.

### **9.3 Objection by minors or incapacitated subjects (if applicable)**

This study is a therapeutic research and will include incapacitated subjects, elderly with a cognitive impairment such as dementia. Whether the patient is participating with this trial or not, all patients who are eligible for this study have to undergo surgery as treatment for the hip fracture. In case of incapacitated subjects informed consent will be received by proxy through the legally representative or a family member. In the unlikely event that incapacitated subject explicitly object to participate, they can leave the study without any further consequences.

#### **9.4 Benefits and risks assessment, group relatedness**

The different approaches in the two treatment arms of the randomised controlled trial are widely used techniques in the Netherlands. At this moment the geographical location where the trauma takes place, will determine in which hospital the patient is operated and which surgical approach they will use. Therefore, there are no extra risks of burden for participating patients. For the patient there will be no large direct benefit of participating to this study. However, the direct lateral approach may leads to a loss of balance due to abductor insufficiency and therefore might increase the risk of falling. This can result in reduced mobility and more vulnerability, asking more of caregivers and/or patients will relying more on home care facilities. The potential value of this research is to maintain the independency of vulnerable elderly patients after hip fractures.

Currently there is a lack of studies investigating the quality and efficiency of care for the elderly and the organization of care, due to the fact that frail elderly patients are frequently excluded in clinical trials. Therefore, the generalizability of most studies is limited and the validity of many guidelines for elderly are inadequate. We think it is paramount to include the frail elderly patients, as they are the majority of the patients who sustain a hip fracture. In our study protocol we followed the guideline for medical research in the elderly(36), that gives guidance to research in this frail patient population.

This guideline concludes that results will be more relevant to medical care for elderly patients, if vulnerability and comorbidity in itself are no longer reasons to exclude patients. Therefore, we think including frail elderly patients is a major asset in our clinical trial.

#### **9.5 Compensation for injury**

The sponsor/investigator has a liability insurance which is in accordance with article 7 of the WMO. The surgery techniques in both treatment arms are widely used in the Netherlands, therefore we will apply for exemption for the insurance for subjects participating in medical research at the consent committee.

#### **9.6 Incentives**

Travel expenses incurred by the participating patients who are visiting the outpatient clinic an extra time are compensated and these costs are budgeted in the financial plan of the study.

## **10. ADMINISTRATIVE ASPECTS, MONITORING AND PUBLICATION**

### **10.1 Handling and storage of data and documents**

All data will be handled according to a data management plan. The multicenter study will generate new quantitative data, which we will be kept for 15 years. The source data will be archived and managed at our academy, the OLVG. All included patients receive a trial code, which anonyms their personal data. The link between the trial code and the patient personal data is saved on a separate secured file with access only by the coordinating investigator.

The handling of personal data will be complied with the Dutch Personal Data Protection Act

### **10.2 Monitoring and Quality Assurance**

A monitoring plan is currently being developed at OLVG (initiating center), and will be applied to this project when ready. Study monitoring will be done using a risk-based strategy.

### **10.3 Amendments**

Amendments are changes made to the research after a favourable opinion by the accredited METC has been given. All amendments will be notified to the METC that gave a favourable opinion. All substantial amendments will be notified to the METC and to the competent authority. Non-substantial amendments will not be notified to the accredited METC and the competent authority, but will be recorded and filed by the sponsor.

### **10.4 Annual progress report**

The sponsor/investigator will submit a summary of the progress of the trial to the accredited METC once a year. Information will be provided on the date of inclusion of the first subject, numbers of subjects included and numbers of subjects that have completed the trial, serious adverse events/ serious adverse reactions, other problems, and amendments.

### **10.5 Temporary halt and (prematurely) end of study report**

The investigator/sponsor will notify the accredited METC of the end of the study within a period of 8 weeks. The end of the study is defined as the last patient's last visit.

The sponsor will notify the METC immediately of a temporary halt of the study, including the reason of such an action.

694

695 In case the study is ended prematurely, the sponsor will notify the accredited METC  
696 within 15 days, including the reasons for the premature termination.

697 Within one year after the end of the study, the investigator/sponsor will submit a final  
698 study report with the results of the study, including any publications/abstracts of the study,  
699 to the accredited METC.

700

701 **10.6 Public disclosure and publication policy**

702 The APOLLO trial is a collaboration between the Dutch Orthopaedic, Trauma and  
703 Geriatric association. We will sign a consortium agreement with all parties concerning the  
704 public disclosure and publication of the research data. Our study protocol and results of  
705 the study will be published in an open access peer reviewed journal, according to the  
706 principles of the publication policy of the CCMO. Thereby, we will register our trial at  
707 [www.clinicaltrials.gov](http://www.clinicaltrials.gov).

708

709

710

711

## 11. STRUCTURED RISK ANALYSIS

Non applicable

